### Analysis of secondary outcomes

#### Time-to-event endpoints

For time to onset/resolution of sore throat (WBS or TCM-assessed) and complete fever resolution time, survival analyses will be conducted using Kaplan-Meier curves to estimate cumulative event probabilities, with between-group comparisons via log-rank tests. Results will be reported as median event times and adjusted hazard ratios (HR) derived from Cox proportional hazards models, accounting for baseline severity and age. Participants lost to follow-up will be censored at their last recorded observation.

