#### Inclusion criteria

Eligible participants must satisfy all criteria:

Age 3–12 years, either sex.

Meeting the above diagnostic criteria for external wind heat syndrome.

Symptom onset within 48 h prior to enrollment.

No use of antipyretics, antibiotics, or antiviral drugs within 24 h before enrollment.

Legal guardian provides written informed consent and agrees to standardized follow-up.

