#### Baseline data

Prior to treatment initiation, comprehensive baseline data will be collected, including demographic characteristics (sex, age, height, weight, ethnicity), medical history (disease duration, past medical conditions, allergies, pre-trial medications), and diagnostic indicators (symptoms such as sore throat and fever, physical signs including pharyngeal/tonsillar erythema, and laboratory results).

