#### Demographic and baseline characteristics

Demographic and clinical baseline characteristics will be summarized by treatment and control group. Categorical variables (e.g., sex, ethnicity, medical history) will be reported as frequency counts (n) and percentages (%), with denominators reflecting available data. Continuous variables (e.g., age, height, weight, symptom duration) will be presented as means ± standard deviations (SD) for normally distributed data or medians with interquartile ranges (IQR) for non-normally distributed data. Missing data counts will be explicitly noted for all variables.

The following baseline parameters will be analyzed:1. Demographics: Age (years), sex (male/female %), height (cm), weight (kg), ethnicity.2. Medical History: Disease duration (days), allergies, pre-trial medications, prior episodes of pharyngitis/tonsillitis.3. Clinical Metrics: Baseline axillary temperature (°C), pharyngeal/tonsillar erythema severity (graded 0–3), laboratory values (WBC, CRP, ALT, AST, Scr).4. TCM Syndrome Scores: Baseline scores for sore throat, dry throat, cough, and pharyngeal signs using the TCM symptom grading scale.

No formal hypothesis testing will be performed for baseline comparisons; results will be interpreted descriptively to evaluate randomization balance.

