### Analysis of primary outcome

Non-inferiority will be evaluated using a predefined margin (Δ = 10%), with the lower bound of the one-sided 97.5% CI for the risk difference (trial-control) between groups compared against −Δ. If this lower bound exceeds −Δ, non-inferiority will be established. The sample size was calculated based on this non-inferiority hypothesis with a one-sided significance level of 0.025, maintaining consistency between design and analysis phases. Between-group comparisons will utilize Chi-square tests for categorical outcomes, supplemented by mixed-effects logistic regression adjusted for baseline covariates (age, baseline WBS score). To ensure consistency in statistical inference, both FAS and PPS analyses must demonstrate non-inferiority to confirm the robustness of conclusions. The trial will be considered successful only when non-inferiority is established for both primary endpoints; therefore, no adjustment for multiple testing is necessary as this represents a conservative approach requiring success on all endpoints. Should non-inferiority be established, superiority testing will be conducted as a hierarchical testing procedure by assessing whether the lower bound of the 95% CI exceeds zero. Results will be reported as proportions, risk differences, and adjusted odds ratios with 95% CIs, with forest plots used to visually represent the treatment effects and their confidence intervals relative to both the non-inferiority margin and zero.

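### Time since symptom onset is collected at baseline but is in none of the named covariate lists; adding it, mainly to the secondary Cox models, would be a small gain in efficiency at almost no cost.

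*Protocol article*

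**What the plan says.** All places are in the protocol article.

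- **Inclusion criteria:** "Symptom onset within 48 h prior to enrollment".
- **Primary and Secondary outcomes:** throat pain is judged at Day 5, and times to onset and resolution come from log cards completed every 24 h after treatment begins. The clock starts at treatment, not at onset of illness.
- **Baseline data:** the items collected include "medical history (disease duration, past medical conditions, allergies, pre-trial medications".
- **Demographic and baseline characteristics:** the item reappears as "Disease duration (days", for descriptive summary.
- **Time-to-event endpoints:** the reported effects are "adjusted hazard ratios (HR) derived from Cox proportional hazards models, accounting for baseline severity and age".
- **Analysis of primary outcome:** the decision is made "with the lower bound of the one-sided 97.5% CI for the risk difference (trial-control) between groups compared against −Δ", with no covariates stated. Chi-square tests are "supplemented by mixed-effects logistic regression adjusted for baseline covariates (age, baseline WBS score").
- **Repeated measures and binary outcomes:** the linear mixed models adjust for baseline value and centre. No covariates are named for the GEE and log-binomial models.

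Duration is also neither a subgroup factor nor a stated stratification factor.

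**The concern.** In a short illness that tends to resolve by itself, time already elapsed at entry should shift the time left to recovery. If treatment starts at enrolment, a Day 5 reading falls anywhere from 5 to 7 days after onset. Baseline pain need not stand in for this: two children with the same score may be at different stages, one worsening and one improving. The article names its covariates explicitly, so the omission is in the text and is not merely a detail left to a fuller plan.

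What is at stake is some power in the adjusted secondary analyses. There is also a point of discipline. Duration will be tabulated by arm, and if the arms differ, an adjustment added at that stage would be post hoc.

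**Working it through.** **1. The plan's own figure.** The sample size section gives expected resolution of 91.43% and 76.92%, margin 0.10, one-sided α 0.025 and power 80%. The unpooled normal formula gives

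n = (0.7692×0.2308 + 0.9143×0.0857) × (1.960 + 0.842)² / (0.1451 + 0.10)² = 33.4, so 34 per group.

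The stated 34 reproduces. It involves no covariates, so nothing below changes it.

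**2. Expected events with 60 per group.**
Resolutions: 60×0.9143 + 60×0.7692 = 101.
Non-resolutions: 120 − 101 = 19.

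**3. How much duration might matter.** The documents give no effect, so this is assumed: lognormal total pain duration with log-SD 0.3 to 0.5; entry delay uniform over 0-48 h among children still ill at entry; calibration so that 76.92% have resolved at Day 5. Day 5 resolution by quarter of the entry window is then:

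| Log-SD | 0-12 h | 12-24 h | 24-36 h | 36-48 h |
|---|---|---|---|---|
| 0.3 | 63.6% | 74.2% | 82.1% | 88.2% |
| 0.4 | 66.9% | 74.9% | 80.7% | 85.5% |
| 0.5 | 69.4% | 75.3% | 80.0% | 83.6% |

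The gradient is visible, but duration explains only about 2-5% of the variance of the Day 5 outcome (R² 0.017 to 0.052).

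**4. Cox model with and without delay.** Same model, 60 per arm, Efron ties, remaining time in the trial arm multiplied by 0.85 (assumed). The gain in squared mean z, which reads as effective sample size, is 9.1%, 6.1% and 3.5% for log-SD 0.3, 0.4 and 0.5. Repeating the simulation moves these by a point or two, so I quote roughly 2-9%.

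**5. Where the gain comes from.** Mean standard errors, without and then with delay:

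| Log-SD | log-HR | log-OR (logistic model) |
|---|---|---|
| 0.3 | 0.203, 0.205 | 0.528, 0.544 |
| 0.4 | 0.204, 0.205 | 0.501, 0.512 |
| 0.5 | 0.205, 0.206 | 0.486, 0.493 |

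The standard errors rise slightly. Hazard and odds ratios are non-collapsible, so the adjusted estimate moves away from the null. At log-SD 0.3 the log-HR goes from about 0.42 to about 0.44, and (0.44/0.42)² × (0.203/0.205)² = 1.098 × 0.981 = 1.08, in line with step 4 given the rounding.

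**6. The risk difference.** Suppose it were adjusted for duration, which the plan does not propose. With assumed odds ratios of 1.5 to 5 per 24 h, its variance falls by about 0-11%, and non-inferiority power changes by at most about 1.5 points. It stays near 97% at the planned rates, and near 26-28% if both rates were 76.92%.

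**The case against.** The strongest case against is that age and baseline severity are a defensible pre-specified set, that nothing in the article is contradictory, and that the benefit is assumed. Much of this stands, and it rules out several stronger readings that a reader might infer.

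- **That the omission widens the intervals.** It does not; step 5 shows the hazard-ratio and odds-ratio intervals becoming marginally wider on adjustment.
- **That chance imbalance eats into the margin.** With delay uniform on 0-48 h, the SD is 48/√12 = 13.9 h. The between-arm difference in mean delay then has SE 13.9×√(2/60) = 2.5 h. An imbalance of about 5 h would move the Day 5 difference by 2.0-3.5 points under the lognormal model, or 1.5-5 points under the assumed odds ratios. But allocation is randomised, and this is ordinary sampling error already covered by the width of the confidence interval. It is neither bias nor inflated type I error.
- **That the primary conclusion is at risk.** The deciding interval names no covariates, and the logistic model only supplements it.
- **That duration is a known strong predictor.** No section says so, and the R² values above are small.
- **That duration is recorded in whole days.** The text gives days as a unit and does not mention rounding. The same section lists symptom duration among continuous variables.

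What the objection does not remove is that a baseline value with a plausible link to every recovery outcome is collected and then left out of every named model.

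**Conclusion.** The point holds as a minor efficiency improvement. Pre-specifying time since onset would give the Cox treatment test roughly 2-9% more effective sample size, through a less attenuated estimate. This rests on the lognormal and uniform-entry assumptions and on a treatment effect of 0.85 on remaining time. The simulation contains no age or severity term, so the gain beyond the covariates already planned was not estimated and may be smaller. The sample size, the validity of the unadjusted comparison and the non-inferiority decision are all unaffected.

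**What to change.** 1. **Time-to-event endpoints:** name time from symptom onset to first dose as a third Cox covariate beside baseline severity and age. With about 101 expected resolutions, one more parameter is harmless in the sore-throat resolution models.
2. **Repeated measures and binary outcomes:** add the same covariate to those models.
3. **Demographic and baseline characteristics:** state that the value is kept in hours or fractional days. Eligibility is already set in hours, so this only makes explicit what the screening check needs.
4. **Analysis of primary outcome:** adding it to the supportive logistic model is optional. With about 19 expected non-resolutions, four terms (treatment, age, WBS, duration) would leave 19/4 ≈ 4.8 per term. The risk-difference test stays as it is.

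The cost is a line on the case report form and a covariate named before unblinding, with no extra patients or visits.

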#### Repeated measures and binary outcomes

Effective/resolution rates at Days 3 and 5 (WBS or TCM-assessed) and TCM symptom-specific scores will be analyzed using generalized estimating equations (GEE) with an exchangeable correlation structure to address repeated measurements. Binary outcomes (e.g., resolution yes/no) will be modeled via log-binomial regression, reporting risk ratios (RR) and 95% CI. Continuous TCM scores will use linear mixed-effects models, adjusted for baseline values and study center.

#### Sensitivity and subgroup analyses

Analyses will be repeated in the per-protocol set to confirm robustness. Missing data will be handled via multiple imputations for sensitivity checks. Subgroup analyses will stratify by age (3–6 vs. 7–12 years) and baseline symptom severity (WBS score ≥7 vs. <7).

#### Safety outcomes and adverse events

Safety analyses will focus on AE incidence, categorized by severity (NCI-CTCAE v5.0 grades 1–5), system organ class, and causality (definite/probable/possible/unlikely related to treatment). AE rates will be summarized descriptively as frequencies (%) within each treatment group, with no formal statistical testing due to expected low event rates. SAEs will undergo detailed case-by-case assessment for potential treatment relationships, with timelines and outcomes documented. All safety data will be analyzed in the SS, comprising participants who received ≥1 dose of the study drug.

## Discussion

This trial aims to provide robust evidence on the effectiveness and safety of XFOL for pediatric acute pharyngitis/tonsillitis (external wind heat syndrome), addressing a critical gap in evidence-based TCM interventions for pediatric upper respiratory infections. By employing a multicenter, double-blind, positive-controlled non-inferiority design with standardized training across sites, the study ensures methodological rigor and generalizability. The integration of both subjective (WBS, TCM symptom scores) and objective outcomes (fever resolution time, laboratory parameters) balances participant-reported experiences with clinically measurable endpoints. Predefined statistical methods, including survival analysis and repeated measures models, enhance the reliability of conclusions.

This trial has several limitations. First, primary outcomes (e.g., WBS-assessed sore throat) rely on subjective participant-reported measures, potentially introducing bias. However, objective metrics such as fever resolution time and laboratory-confirmed inflammatory markers (e.g., CRP) are incorporated to balance subjective assessments. Additionally, though non-inferiority tests can be used to confirm XFOL efficacy relative to the comparator, it is also necessary to conduct an analysis of the advantages and disadvantages of the XFOL. Compared with the positive control drug XYG, the advantage of XFOL lies in its composition, which enables it to comprehensively exert the effects of clearing heat and dispersing wind, as well as to reduce swelling and fever, relieve sore throat, and improve tonsil enlargement. On the other hand, its limitations include relatively weak efficacy for other types of throat diseases and limited research data on its long-term efficacy and safety. Despite these limitations, the trial’s multicenter design, standardized training across sites, and predefined statistical analysis plan enhance methodological rigor. Results will provide critical evidence for integrating TCM into pediatric care, addressing unmet needs in acute upper respiratory infection management.

Our study makes contribution to supplement current international reporting in the following three aspects. Firstly, it establishes a more scientific and rigorous scientifically rigorous statistical analysis framework for international reports, especially in the context of traditional Chinese medicine clinical trials, by providing solutions for reasonable sample size estimation, analysis methods for primary and secondary endpoints, and handling of missing data. Subsequently, this study establishes a novel hybrid evaluation model by integrating an efficacy framework that combines TCM syndrome scoring with pediatric-specific tools including the Wong-Baker FACES scale and age-stratified dosing. Finally, our study will supply extensive data and analysis report on the safety of XFOL in treating pediatric acute pharyngitis/tonsillitis.

## Conclusion

In summary, this multi-center, randomized, double-blind, positive-controlled, non-inferiority trial will evaluate the effectiveness and safety of XFOL for pediatric acute pharyngitis/tonsillitis. By implementing a pre-registered statistical analysis plan, the study will ensure methodological transparency and minimize the risk of outcome reporting bias, providing a robust framework for assessing Fengreqing Oral Liquid. Predefining endpoints, analysis populations, and non-inferiority criteria will safeguard against data-driven conclusions and enhance reproducibility.

We argue that this study will significantly contribute to the evidence-based integration of TCM into pediatric care.
